# Efficacy of verum and sham acupoint catgut embedding for treatment of obesity: Study protocol for a randomized controlled trial

**DOI:** 10.1186/s13063-019-3730-8

**Published:** 2019-11-27

**Keywords:** Acupoint catgut embedding, Obesity, Randomized controlled trial, Visceral fat area

## Abstract

**Background:**

Obesity has become a major public health hazard with epidemic proportions, affecting adults, adolescents, and children of both genders. Previous studies have suggested that acupoint catgut embedding (ACE) might be a potential therapeutic approach for obesity. The purpose of this study is to conduct a rigorous and normative trial to determine the efficacy of ACE for obesity.

**Methods/design:**

A total of 99 eligible patients diagnosed with obesity will be recruited in this study. They will be randomly allocated to either the verum ACE group, sham ACE group, or waiting list (WL) group, with 33 patients in each group. Each patient in the two ACE-based groups will receive eight sessions of treatment, lasting over 8 weeks. The primary outcome is the reduction of body mass index (BMI) after treatment. Secondary outcomes will include waist circumference (WC), hip circumference (HC), waist:hip ratio, body fat percentage, blood lipid level, subcutaneous fat area, visceral fat area, and World Health Organization Quality of Life (WHOQOL). All the outcomes will be evaluated at baseline, at the end of the 8 weeks of treatments, and at 3 months of follow-up. The evaluators and data analyzers will be blinded to group allocation.

**Discussion:**

The findings of this randomized, sham-, and WL-controlled trial will help to investigate the influence of ACE on clinical variables as well as visceral fat area of obesity, which will provide high-quality evidence on the efficacy of ACE for obesity.

**Trial registration:**

Chinese Clinical Trial Registry, ChiCTR1800020248. Registered on December 21, 2018.

## Background

Obesity is an increasing global public health issue characterized by the rise of body fat tissues. Genetic, dietary, lifestyle, and environment factors can all induce obesity. The prevalence of obesity has doubled over the past 10 years [1]. In 2015, in the US, more than 20% of the population was identified to be overweight or obese, being very common in adults [2]. According to Global Health Observatory (GHO) data released in 2016, 39% of adults suffered from overweight or obesity. To date, the prevalence of obesity is increasing in both developed and developing countries. Obesity is associated with increased risk for developing a range of comorbid conditions, such as type 2 diabetes (T2D) [3], cardiovascular disease (CVD) [4], fatty liver disease, and gastrointestinal and psychological disorders [5]. For instance, a number of scholars have reported that obese adults showed a 50% increased risk of developing T2D compared with normal-weight adults [6] and were twice as likely to have hypertension and CVD [7]. Nowadays, obesity and its complications impose a heavy burden on socio-economic development; the World Health Organization (WHO) considers obesity as one of the most serious public health problems worldwide [8, 9].

Methods to treat obesity such as lifestyle modification (specifically dietary modification and regular exercise), surgery, drugs, and complication therapy, are all referred to by the guidelines released by the National Heart, Lung and Blood Institute (NHLBI) of National Institutes of Health (NIH), American College of Cardiology (ACC), etc. [10]. The primary and the most valid recommendations for treating obesity are to restrict the intake of high calorie diets and more physical activities. However, these two methods are often challenging for patients to adopt long-term due to lifestyle and economic issues [11]. Additionally, according to the Cochrane Database of Systematic Reviews, there is no sufficient evidence to indicate that the short-term adjustment of food consumption and physical activity leads to long-term weight loss [12, 13]. On the other hand, anti-obesity drugs seem to be questionable in terms of their efficacy and safety as the adverse events (AEs) associated with these drugs often have negative consequences, such as headache, dizziness, nausea and vomiting, insomnia, etc. The US Food and Drug Administration (FDA) in 2010 [14, 15] recommended against and prohibited the use of some anti-obesity drugs because of serious liver damage and the high risk of CVD. Additionally, rimonabant was found to induce anxiety, depression, and other mental disorders [16]. Consequently, identification of effective and low-risk interventions is highly essential for obese individuals.

Acupoint catgut embedding (ACE), a complementary and alternative therapy, has been used for several decades to treat a variety of disorders, such as perimenopausal syndrome, chronic urticaria, depressive disorder, refractory insomnia, obesity, sciatica, etc. [17]. ACE involves the weekly infixing of surgical chromic catgut sutures into the subcutaneous tissue of the extremities and abdomen with a specialized needle under aseptic conditions. Owing to the continuous acupoint stimulation by the implanted sutures, ACE was considered to be more effective than ordinary acupuncture or electroacupuncture for patients with obesity [18]. Previous research revealed that the body weight and body mass index (BMI) of obese patients could be remarkably decreased after ACE therapy [19]. Moreover, ACE could adjust the imbalance of obesity-related hormones, e.g., leptin, ghrelin, and adiponectin, to reduce body weight [19, 20]. In addition, visceral fat accumulation is often accompanied by obesity, which has been recently reported to play a vital role in the development of metabolic syndrome, a cluster of diabetes, dyslipidemia, and hypertension [21]. A randomized controlled trial (RCT) conducted by Lei et al. [22] revealed that electroacupuncture treatment could reduce BMI and waist circumference (WC), as well as visceral fat area (VFA). However, whether ACE can improve the VFA of obese patients and what the relationship is between VFA and obesity-related indices are still uncertain. Only a limited number of RCTs have investigated VFA changes with regard to ACE treatment for obesity.

Hence, this study is designed as a RCT to assess the effectiveness and safety of ACE for treatment of obesity.

## Methods/design

### Study design

This single-center, randomized, sham-controlled trial will be conducted at Shenzhen Traditional Chinese Medicine Hospital (Shenzhen, China). The study protocol was approved by the Ethics Committee of Shenzhen Traditional Chinese Medicine Hospital. The study will be conducted in accordance with the 1975 Declaration of Helsinki and the Standard Protocol Items: Recommendations for Interventional Trials 2013 Checklist (Additional file 1). A flowchart of the research procedure is shown in Fig. 1.

**Fig. 1 Fig1:**
[figure not shown]
Flowchart of the study design

### Patient recruitment

Patients who meet the inclusion criteria will be mainly recruited through outpatient clinics, online or offline advertisements (e.g., newspaper, poster, websites), or the WeChat public account of Shenzhen Traditional Chinese Medicine Hospital. If a patient is interested in joining the study, he/she can contact and consult with one of the researchers. Those patients who meet the inclusion criteria will be involved in the study. All the participants will sign a written informed consent form prior to the start of the study. The schedule of patient enrolment, intervention, and assessment is illustrated in Fig. 2.

**Fig. 2 Fig2:**
[figure not shown]
Study schedule for data collection

### Inclusion criteria

Inclusion criteria are as follows:
Diagnosed with obesity according to Asian adult BMI criteria defined and proposed by the WHO Western Pacific region obesity working group in 2000WC of ≥ 90 cm for males or ≥ 80 cm for femalesAged 18 to 65 years oldDoes not have any taboos regarding catgut embedding therapyCompletes written informed consent

### Exclusion criteria

Patients with any one of the following criteria are excluded from this trial:
Endocrine disease (thyroid disease, pituitary disease, and diabetes mellitus) and autoimmune disease (systemic lupus erythematosus, Sjogren’s syndrome, and rheumatoid arthritis)Metabolic disease such as hypertension and dyslipidemiaOther methods being used to control body mass and abdominal circumference, such as surgery, drugs, etc.Women in pregnancy, nursing, perimenopauseSome severe diseases of the heart, liver, and kidney, or has tumorDiagnosed with a psychiatric disorderParticipated in another study within 3 months

### Dropout criteria

Patients who do not meet the inclusion criteria but are mistakenly enrolledOccurrence of severe AEs or complications which result in stopping the trial

### Sample size

The sample size has been calculated on the basis of results from a previous clinical trial [19]. The primary outcome in the present study is BMI reduction from baseline following 2 months of treatment. According to a previous study [19], in the ACE group, the BMI decreased 1.65 (standard deviation (SD) 1.24); in the sham ACE group, the BMI reduced 0.38 (SD 1.51). Considering a two-sided significance level of 0.05 and power of 0.90, 26 participants in each group are required as calculated by *t* test in G*Power software (version 3, Institute for Experimental Psychology, Heinrich-Heine-University, Germany). A dropout rate of 15% was taken into account so a total of 99 participants will be recruited in this trial (*n* = 33 participants in each group).

### Randomization and allocation concealment

If the participants meet all the inclusion criteria and sign the written informed consent form, they accept the principle of random allocation. Hence, 99 eligible participants will be randomly assigned to the verum ACE group, sham ACE group, and waiting list (WL) group at a ratio of 1:1:1. A random allocation sequence number will be generated using Statistical Analysis System software (SAS, version 9.1.3, SAS Institute Inc., Cary, NC, USA) by an independent statistician who will not be involved in the treatment or data collection. The sequential numbers are written on cards and sealed in an opaque envelope by an independent research assistant. After a participant randomly selects an opaque envelope and obtains an allocation sequence number, a research assistant will assign an identification code to them and record them in a case report form (CRF). Then, the result of a patient’s allocation will be given to the acupuncturists.

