### WL group

The WLC group will not have any intervention. The patients will be asked to receive delayed ACE therapy for free after a waiting period of 20 weeks.

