### Data management and monitoring

The research associates will record the information on the CRFs and verify that the data is fully, swiftly, and accurately collected. The private information and medical records of patients, including their name, phone number, and ID number, will be anonymous to ensure confidentiality. All the research documents will be kept in specialized cabinets and preserved for at least 5 years after publication.

In addition, a data monitoring committee is established consisting of experienced experts in the Good Clinical Practice Department of the Shenzhen Traditional Chinese Medicine Hospital to periodically review the progress of the trial and monitor collection of the data, allocation concealment, etc. The modification or termination of the trial can be performed by the committee. The data monitoring committee is independent from the sponsor and has no conflict of interest.

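### Participants choose their own envelope, and the ID code and CRF entry follow the draw, so the SAS order goes unused and a returned and repeated draw would be hard to detect

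*Protocol article*

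**What the plan says.** All steps come from the section on randomization and allocation concealment unless noted.

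- **Entry:** eligibility and consent come first: "If the participants meet all the inclusion criteria and sign the written informed consent form, they accept the principle of random allocation".
- **Sequence:** the list for 99 participants at 1:1:1 is generated in SAS "by an independent statistician who will not be involved in the treatment or data collection".
- **Envelopes:** "The sequential numbers are written on cards and sealed in an opaque envelope by an independent research assistant". No number on the outside is described.
- **Draw and registration:** "After a participant randomly selects an opaque envelope and obtains an allocation sequence number, a research assistant will assign an identification code to them". The same sentence then has the research assistant enter the participant in the CRF.
- **Release:** "Then, the result of a patient’s allocation will be given to the acupuncturists".
- **Waiting list (WL group section):** this arm receives no intervention during the trial period. "The patients will be asked to receive delayed ACE therapy for free after a waiting period of 20 weeks".
- **Oversight (Data management and monitoring):** a data monitoring committee is "to periodically review the progress of the trial and monitor collection of the data, allocation concealment, etc".

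**The concern.** Sealed envelopes protect allocation best when each can be used only once, in a fixed order, by a person already identified. The stated procedure gives up two of these features. The participant's choice replaces the list order, so nothing says which allocation the next participant should have received. The participant is also not tied to an envelope before obtaining the number, so the described records would look the same whether the first or a second draw was kept.

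There is a foreseeable motive to redraw. One arm is an open waiting list with a 20-week delay, in a trial that recruits partly through advertisements. If people who dislike waiting are moved out of that arm, those who remain are a selected group. The Discussion relies on the untreated group to gauge non-specific effects (sham against no intervention), and an analysis could not reliably correct such selection afterwards.

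**Working it through.** No figure in the plan describes this risk, so the check is mainly a comparison of the stated steps, with one small calculation on an assumed rate.

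**1. Order of steps.** Eligibility and consent → participant selects an envelope → number obtained → ID code → CRF entry → result passed to the acupuncturists. The only stated record of the individual that precedes the draw is the signed consent form.

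**2. What the stated records could show.**

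| Event | Would it show? |
|---|---|
| Card drawn and lost or kept | Yes: reconciling cards and CRFs with the SAS list leaves a number unaccounted for |
| Participant leaves after drawing | Yes: a signed consent without a CRF. If the card went back into the pool, the arm drawn would not be known |
| Card put back and another drawn | Hardly: one consent, one CRF, one number, and no expected order to contradict it |

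**3. Final counts.** Assume 99 envelopes, 99/3 = 33 per group, all eventually used. A returned card stays in the pool and goes to someone else, so the totals are 33/33/33 with or without redraws.

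**4. Counts early in recruitment.** Suppose a fraction p of waiting-list draws is put back and redrawn once from the full set. The documents give no value for p, so a range is shown. The waiting-list share of a first draw is

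(1/3)(1 − p) + (1/3)·p·(1/3) = (1 − p)/3 + p/9.

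| p (assumed) | Waiting-list share |
|---|---|
| 0 | 33.3% |
| 0.05 | 0.95/3 + 0.05/9 = 32.2% |
| 0.10 | 0.90/3 + 0.10/9 = 31.1% |
| 0.20 | 0.80/3 + 0.20/9 = 28.9% |

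Shifts of about 1 to 4 percentage points would be hard to see in interim counts of a trial of 99. The table shows how poorly counts detect redraws. It does not estimate how many occur.

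**5. Which comparison is exposed.** The Sample size section builds its calculation on the verum and sham figures, so that is the powered comparison. Verum and sham have equal numbers of envelopes, so a participant who returns a waiting-list card and then draws an active card is equally likely to get either. Avoiding the waiting list therefore does not systematically separate verum from sham. It does change who is in the waiting list, and so affects both comparisons with it.

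**The case against.** The strongest defence is that the essentials of concealment are present. The list is generated independently, the cards are sealed in opaque envelopes by an independent person, and a blind draw from a finite set still gives random allocation. Consent precedes the draw, the Quality control section requires withdrawals to be recorded in detail, and an independent committee monitors allocation concealment. Nothing permits a redraw. The card is said to carry a sequence number, and the text does not say that it shows the group. If it does not, the participant may be registered before anyone present knows the arm, which makes a selective redraw harder.

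Most of this stands, and it rules out two stronger readings. A reader might infer that concealment cannot be audited at all. The documents do not support that: a finite set of numbered cards can be reconciled with the SAS list and the CRFs. A reader might also infer that a participant can draw the waiting list and leave without trace. That fails because a signed consent form already exists.

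The defence does not answer the returned card. Reconciliation finds missing cards, not exchanged ones, and the committee has no expected order to check against. Nor is this merely detail left to a fuller document: the article states free selection first and registration second. That no envelope log is described is, by contrast, no finding, since an article may leave that out.

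**Conclusion.** The point holds as a weakness in the stated procedure. Free choice of envelope discards the order of the SAS sequence, and with ID code and CRF entry only after the number is obtained, a returned and repeated draw would be hard to detect.

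Its size is unknown and cannot be derived from the document. That redraws might happen is inferred from the order of steps; the document neither permits nor reports them. The risk is greatest if the card, or someone present at the draw, reveals the group, and the text is silent on this. The statement that end-of-trial totals would be uninformative assumes 33 envelopes per group, all used.

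The main exposure is in comparisons with the open waiting list. A reader might extend the concern to the powered verum-sham result, but the foreseeable motive is to avoid waiting, and a redraw made for that reason falls on verum or sham by chance.

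**What to change.** Reverse the order and remove the choice:

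1. Complete eligibility, consent and baseline measures.
2. Assign the ID code and make the CRF entry.
3. Take the next sequentially numbered, sealed opaque envelope in strict order, write the ID and date on it, and only then open it. The participant does not choose.
4. Reconcile the used envelopes against the SAS list, which gives the data monitoring committee an expected order to check.

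The sequence number has to appear on the outside of each envelope, applied by the independent person who seals them. The protocol should also say whether the card shows the group.

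Patients already randomised keep their allocation. For them, compare signed consents with CRFs once, and report anyone who left after drawing as randomised, with the arm where it can be established.

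The change is a one-paragraph amendment, reported to the Ethics Committee as the protocol requires. It needs no additional staff and leaves arms, outcomes and sample size unchanged. The cost is a slightly less convenient enrolment visit. The article describes the trial as still recruiting, so later enrolments would benefit.

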### Blinding

The acupuncturists are not blinded for the entire process. To eliminate potential bias, outcome assessors and statisticians are blinded to group assignment. Patient allocation will only be revealed under some special conditions, such as severe allergy, serious infection, uncontrolled pain, etc.

### Interventions

The ACE intervention is compliant with the Standards for Reporting Interventions in Clinical Trials of Acupuncture (STRICTA) guidelines. Patients in the verum ACE group, sham ACE group, and WL group will receive real ACE therapy, sham ACE therapy, and delayed active ACE therapy 20 weeks later, respectively. The course for the two ACE groups will comprise eight sessions over 8 weeks (one session per week).

### Verum ACE group

#### Acupoints

ACE treatment is a semi-standard method in this study. According to clinical practice, the literature, and the basic theory of traditional Chinese medicine, the prescription of ACE includes six obligatory acupoints and two groups of adjunct points.

The obligatory acupoints will include RN 12 (Zhongwan), ST 25 (Tianshu), SP 15 (Daheng), RN 06 (Qihai), RN 04 (Guanyuan), and GB 26 (Daimai). Adjunct acupoints will consist of two groups: acupoints of group 1 involve ST 36 (Zusanli), SP 09 (Yinlingquan), and ST 40 (Fenglong); acupoints of group 2 include BL13 (Feishu), BL20 (Pishu), and BL23 (Shenshu). The obligatory acupoints will be chosen in each session, and the adjunct points will be selected every other session. All acupoints will be localized according to the names and locations of acupoints drafted in 2006 by the National Standard of the People’s Republic of China (GB/T 12346–2006). Locations of the acupoints are presented in Table 1 and Fig. 3.

**Table 1 Tab1:** Locations of acupoints in the two ACE groups

Acupoints	Locations
RN 12 (Zhongwan)	On the anterior median line, 4 cun above the umbilicus
ST 25 (Tianshu)	Level with the umbilicus, and 2 cun lateral to the anterior median line
SP 15 (Daheng)	Level with the umbilicus, and 4 cun lateral to the anterior median line
RN 06 (Qihai)	On the anterior median line, 1.5 cun below the umbilicus
RN 04 (Guanyuan)	On the anterior median line, 3 cun below the umbilicus
GB 26 (Daimai)	On the lateral abdomen, at the intersection of the vertical line of the free end of the 11th rib and the horizontal line on the same level of umbilicus, or 1.8 inch below LR 13 (Zhangmen) at the liver meridian
ST 36 (Zusanli)	3 cun directly below ST 35 (Dubi), and 1 digit lateral to the anterior margin of the tibia
SP 09 (Yinlingquan)	On the medial side of the calf, in the sunken spot between the medial lower margin of the tibia and the medial margin of the tibia
ST 40 (Fenglong)	8 cun directly below ST 35 (Dubi), and 2 digits lateral to the anterior margin of the tibia
BL13 (Feishu)	On the back, on the same level of the third subspinous of thoracic spine, and 1.5 cun lateral to the posterior midline
BL20 (Pishu)	On the back, on the same level of the 11th subspinous of thoracic spine, and 1.5 cun lateral to the posterior midline
BL23 (Shenshu)	On the back, on the same level of the second subspinous of lumbar vertebra, and 1.5 cun lateral to the posterior midline

**Fig. 3 Fig3:**
[figure not shown]
Locations of acupoints

#### Preparation of ACE

Catgut (Suzhou medical Co. Ltd, Jiangsu, China) of length 1.5 cm will be placed in front of an embedded needle (Zhengjianggaoguan medicine Co., Ltd., Shenzhen, China) for the operation. ACE will be performed under sterile conditions.

#### Operation procedures of ACE

Firstly, the acupuncturist should disinfect their hands with 75% alcohol and don medical gloves, medical mask, and medical hat. Simultaneously, patients will lie on the bed, supine or in a prone position according to the location of the acupoints, and will fully expose the skin of the acupoint area. Secondly, the acupoint regions will be sterilized with iodophor and alcohol twice by the acupuncturist. Simultaneously, an assistant will place the catgut in front of an embedded needle. Thirdly, the acupuncturist will locate the acupoint and then embed the needle into the skin at the appropriate place; consequently, the catgut will be embedded into the acupoint at a depth of about 1.5, 1, or 1 cm at the abdomen, lower limbs, and back, respectively. The embedded needle will be withdrawn once the patient has a feeling of soreness (*Deqi*); the catgut will be left under the tissue. Following this, sterile cotton balls will be pressed onto the acupoint for hemostasis and band-aids will be applied to the acupoints to prevent wound infection. Patients will be warned to avoid getting water on the embedded acupoints for 24 h.

The frequency of the ACE treatment will be once per week, lasting a total of 8 weeks.

